## Abstract

Multiple approaches can be used to communicate public health messages through mass media. It is unclear which approaches are superior for meeting the needs of the general community along with vulnerable population subgroups. To compare different public health strategy communication approaches for influencing the COVID-safe behavioural intentions of both community and vulnerable population subgroups. This study will conduct three concurrent ‘helix’ randomised controlled trials with Latin square sequencing and factorial intervention allocation to assess the effectiveness of different communication strategies amongst the Australian general community and six subgroups that are considered vulnerable to contracting, transmitting or experiencing severe consequences of COVID-19 infection. Communication approaches being compared include: the format of communication (written versus video), who is providing information (general practitioner, politician, community-representative), what is said and how it is delivered (direct information provision versus conversational approach) and the visual content of video messaging (animation versus ‘talking head’). Recruited participants will be randomly allocated to receive a specific combination of health messaging strategies using six different COVID-19 context areas. Outcomes will be assessed in a survey using behaviour intention questions, and questions surrounding level of agreement with feeling represented in the health messaging strategy. These trials will use a unique research approach to provide an experimental evidence base to help guide development of impactful and inclusive COVID-19 and related public health messaging. All three trials are registered with the Australian New Zealand Clinical Trials Registry (ANZCTR). Trial 1: Update and impact of Government recommendations about COVID-19 (coronavirus)-Stage 3, Trial 1, vulnerable subgroup populations (ACTRN12622000606785). Trial 2: Update and impact of Government recommendations about COVID-19 (coronavirus)-Stage 3, Trial 2, community group (ACTRN12622000605796). Trial 3: Update and impact of Government recommendations about COVID-19 (coronavirus)-Stage 3, Trial 3, What communication strategy is most effective for both vulnerable and community group populations? (ACTRN12622000617763).

## Introduction

### Background and rationale

Informative public health messages have been widely used as a part of the global COVID-19 response [1, 2]. Research conducted since the beginning of the COVID-19 pandemic has highlighted the disparity that exists in health outcomes of the general population compared with vulnerable communities [3–8]. It has been argued that public health messages need to address the various needs (including healthcare, communication and cognitive considerations), as well as the health literacy and sociocultural factors relevant to vulnerable communities, in order to reach these communities effectively [7, 9–12]. There are several dimensions by which public health messaging can be varied, which may have an impact on its effectiveness. These can include: the format of communication (written versus video), who is providing information (general practitioner, politician, community-representative), what is said and how it is delivered (direct information provision versus conversational approach) and the visual content of video messaging (animation versus ‘talking head’).

How people access information has changed rapidly in recent years. It is estimated that by the end of 2022, internet video traffic will be 82% of all consumer internet traffic (up from 73% in 2017) [13]. This highlights the potential instinctive preference for consumers to choose to receive health information via video format compared with written information. Previous research has indicated that older adults respond more positively to information presented in video format compared to equivalent written information and tend to prefer video format via television news programs [14, 15]. Similarly, younger people who are more exposed to social media platforms, such as YouTube and Facebook, will be more likely to view public health messaging in video format, as these are largely video based platforms which allow users to quickly and easily view and share content [14, 16]. While research has aimed to identify the preferred format of receiving health information (video versus written), the effectiveness of either has yet to be strongly established, and in Australia, the Commonwealth Department of Health has continued to use both methods during the pandemic [17]. Further research is required to better establish not only the preference, but more importantly the effectiveness of written public health messaging compared to video based public health messaging, for the general Australian community.

The issue of ‘who’ provides the public health message is an important consideration in ensuring that it is effective [18, 19]. During the COVID-19 pandemic there has been a range of spokespeople providing public health messaging, including politicians, jurisdictional medical officers, scientists, general practitioners and other health professionals, and community representatives [1, 20]. Previous work has shown trust to be a key factor in the acceptance and adoption of COVID-safe behaviours such as physical distancing, staying at home when you are unwell and other prevention guidelines [19, 21]. These studies suggest people tend to have a higher level of trust in scientists and health professionals conveying COVID-19 health recommendations (compared to politicians), and are more likely to implement COVID-safe behaviours recommended to them by scientists, compared to recommendations provided by politicians who they trust less [19, 21–23]. Trust in health professionals, such as general practitioners, has also been seen to impact vaccine uptake in minority ethnic groups in the United Kingdom [24]. Similarly, some qualitative work has indicated that culturally and linguistically diverse groups respond more positively to health messages delivered by community representatives, as they are more trusted [25]. During the COVID-19 pandemic, the Australian Government created health information videos presented by various representatives within the community. Some of these included, government representatives (for example, chief medical officers), general practitioners and community representatives. Although ‘who’ presents the message has been varied, it is not yet known ‘who’ is preferred or how effective these videos are in eliciting positive behavioural change in both the general Australian community and vulnerable subgroup populations. There is also further need to understand how bringing about behaviour change for vulnerable subgroup populations may differ from the ways that this is achieved for the general Australian community.

How a given spokesperson communicates a public health message may also be of importance. Some videos may take a direct, information provision approach, such as a public service announcement [26]. Others might use a more conversational approach, such as providing relatable advice, or through the use of a narrative [27]. These approaches and many others have been used by advertisers, health authorities and governments internationally throughout the COVID-19 pandemic [28–30]. It has been suggested that direct information provision strategies may not achieve their desired effect, particularly in areas with low levels of trust in the government [31]. Conversely, communication that is empathetic and uses a narrative style is argued to be a more effective approach [32, 33]. While this may be true for the general community, research regarding which information provision approach has the greatest impact and effectiveness for vulnerable subgroup populations is still lacking.

A further dimension to be considered in public health messaging is the visual content or imagery used while the message is being conveyed. Some videos use a piece to camera, or ‘talking head’ approach, where a person of relevance presents information as if talking to the audience, generally remaining on-screen for the majority of the video [34]. An alternative approach is showing an animation as the visual content, with voice over. The Australian Government has used both methods during the COVID-19 pandemic [34, 35]. The talking head approach has been argued to have varied effectiveness, depending on who is delivering the message and the public’s level of trust in that person [31]. Previous research has indicated that using animation can lead to increased COVID-19 knowledge, compared with no intervention [36]. It has also been suggested that increased exposure to animation leads to increased recall of the health information [37]. Therefore, it would be useful to ascertain which visual content has the greatest impact on vulnerable populations.

Public health messaging campaigns have many dimensions to their success. Understanding these dimensions in greater detail is important in ensuring an effective and cost-effective campaign is produced, leading to the greatest uptake in positive health behaviours. This research will investigate the effects of delivering COVID-19 public health messaging to the Australian community as well as six vulnerable subgroup populations in multiple formats. Differences include written versus video-based information provision as well as differences in the production of each video. Videos will differ in who presents the information (general practitioner or a community group representative), how the message is conveyed (direct information provision or conversational approach), and what is seen on-screen (animation or talking head).

### Objective

This protocol outlines the design and methods for three concurrent ‘helix’ randomised controlled trials to investigate how to best deliver a health message to all Australians (vulnerable and general community groups). Specifically, we seek to investigate the importance of:

Who provides public health messages (general practitioner, politician, community leader)The visual imagery used in public health messages (talking head versus animation)The format of public health messages (written versus video)How a public health message is delivered (conversation training versus information provision)

on the outcomes of intention to follow COVID-safe behaviours, likelihood of encouraging others to follow COVID-safe behaviours, and perception of being represented in the public health message.

## Materials & methods

### Design

The Standard Protocol Items: Recommendations for Interventional Trials (SPIRIT) flow diagram schedule of enrolment, interventions and assessment procedures is provided in Fig 1 [38]. We will conduct three concurrent ‘helix’ randomised controlled trials (Figs 2–4), as approved by Monash University Human Research Ethics Committee on the 8^th^ April 2022 (HREC 30698). The Helix design is a counterbalanced, randomised controlled trial that involves allocating participants to each level of an intervention, but spread across different context areas. The outcome measure is repeated for each intervention level / context area exposure, allowing for a pooled analysis with repeated measures within participants. This enhances statistical power of an investigation while minimising the risk of intervention-level contamination by separating them across the different context areas.

**Fig 1 pone.0280865.g001:**
[figure not shown]
SPIRIT flow diagram: Schedule of enrolment, interventions, and assessment procedures.

**Fig 2 pone.0280865.g002:**
[figure not shown]
Visual representation of the helix randomised control trial design for Trial 1. C1 denotes combination 1, C2 denotes combination 2, C3 denotes combination 3, C4 denotes combination 4. Individual participants are exposed to the combinations of intervention level / context areas within a vertical combination column.

**Fig 3 pone.0280865.g003:**
[figure not shown]
Visual representation of the helix randomised control trial design for Trial 2. C1 denotes combination 1, C2 denotes combination 2, C3 denotes combination 3, C4 denotes combination 4. Individual participants are exposed to the combinations of intervention level / context areas within a vertical combination column.

**Fig 4 pone.0280865.g004:**
[figure not shown]
Visual representation of the helix randomised control trial design for Trial 3. C1 denotes combination 1, C2 denotes combination 2, Individual participants are exposed to the combinations of intervention level / context areas within a vertical combination column.

In trial 1, we will combine the ‘helix’ approach with factorial allocation of intervention levels. In all trials we will be using Latin-square sequencing of the intervention levels to minimise the risk of order effects from potentially biasing the contrasts between intervention levels. Participants will be exposed to context areas in a set order (meaning that order effects could impact contrasts between them) as comparisons between contexts are not of primary interest in these investigations.

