#### Trial 3 (all participants)

Trial 3 will include two intervention arms across two different context areas related to COVID-19 health. The two arms of the study will be:

Conversational training approach provided by a general practitioner (talking head).Direct information provision provided by a general practitioner (talking head).

The arms of study differ by the language, content and tone. The conversational training approach provides a health message in a peer-to-peer fashion that is expressed in a relaxed conversational tone. The direct information provision arm, provides a health message that is direct and didactic in style, and does not provide suggested statements that people could say in a discussion with another person on this topic.

The two context areas will be:

Encouraging people who have workers coming to visit them at home to ask them if they are vaccinated or not.Encouraging people to avoid sharing food, utensils and other items at gatherings.

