### Study timeline

Participants will be able to access the relevant survey (to their subgroup) leading to either Trial 1 then Trial 3 (combined) or Trial 2 then Trial 3 (combined) independently or with assistance from the corresponding Partner Organisation. By following the link to the corresponding survey for each subgroup population, participants will have access to the explanatory statement including inclusion and exclusion criteria. From there, participants can choose to participate and confirm they adhere to the inclusion criteria. The data collection and survey builder software Qualtrics (Qualtrics, Provo, UT, USA) will automatically, randomly allocate participants into one of four potential combinations of allocation using a Latin Square approach for both Trial 1 and Trial 2, (minimising study level order effects), and will again randomly assign to one of two possible combinations for Trial 3. Data will be extracted for analysis purposes with no follow-up period required. Refer to Fig 1 for an overview of the study timeline.

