### Analysis

The comparisons we will undertake across the three trials will be:

#### Trial 1

Main effect of who is providing the message (General Practitioner versus community representative).Main effect of visual stimulus (talking head versus animation).Interaction effect between these two main effects.Simple effects if interaction effect is significant.

#### Trial 2

General practitioner talking head visual stimulus delivered health message versus animated general practitioner visual stimulus delivered health message.Politician visual stimulus delivered health message versus general practitioner talking head visual stimulus delivered health message.Written delivery of health message (control) versus all other intervention types (general practitioner talking head, general practitioner animation and politician delivered health message).

#### Trial 3

The effectiveness of health information provision delivered through a conversational training approach by a general practitioner versus through a direct information provision approach by a general practitioner.

Comparisons will not be made between context areas as part of the primary analysis. However, we will investigate interaction effects of the different intervention comparisons across the different context areas and population subgroups so that we can understand whether certain interventions work better in certain contexts and populations.

Linear mixed model analyses will be used treating the intervention levels as fixed factors and participants as random factors. Context will be ignored when investigating intervention main effects as it will be balanced across the different intervention levels.

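### Contexts shown in one set order: the planned intervention-by-context interactions cannot be separated from intervention-by-position effects or, in Trial 3, from sequence and carry-over

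*Protocol article*

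**What the plan says.** In Materials & methods, Design (the paragraph after the Fig 4 caption), the protocol uses "Latin-square sequencing of the intervention levels to minimise the risk of order effects from potentially biasing the contrasts between intervention levels". Contexts are treated differently: "Participants will be exposed to context areas in a set order (meaning that order effects could impact contrasts between them". The reason given is "as comparisons between contexts are not of primary interest in these investigations".

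The Study timeline states how many allocations there are. The platform will "randomly allocate participants into one of four potential combinations of allocation using a Latin Square approach for both Trial 1 and Trial 2", and "will again randomly assign to one of two possible combinations for Trial 3". The Interventions section adds that "Trial 3 will include two intervention arms across two different context areas related to COVID-19 health".

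The Analysis section leaves context out of the models for intervention main effects, on the ground that it is balanced over intervention levels. It then says "we will investigate interaction effects of the different intervention comparisons across the different context areas and population subgroups", and gives the purpose: "so that we can understand whether certain interventions work better in certain contexts and populations". It attaches no caveat about order to that plan.

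**The concern.** The reason given for the set order covers one kind of comparison, context against context. The Analysis section plans another kind, in which the effect of an intervention is compared between contexts, and it means to give the answer a substantive reading. If the second context is always the second message, a result that animation gains more in one context than in another can also be read as animation gaining more at one place in the sequence than at another. At stake is the context half of a stated analytic aim: advice on which communication approach suits which COVID-safe behaviour.

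**Working it through.** The protocol gives no figure for these interactions, so there is none to reproduce. The only sample-size input used is 40 per vulnerable subgroup, which follows from 36/(1 - 0.10) = 40 (Sample size).

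**Inputs.** One context order for all (Design); four combinations in Trials 1 and 2 and two in Trial 3 (Study timeline); four intervention levels over four contexts in Trials 1 and 2, two arms over two contexts in Trial 3 (Interventions). Figs 2 to 4 are not shown and the particular Latin square is not given. Cyclic and Williams squares were both tried and gave the same ranks.

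**Rank check.** Build the design matrix of cell means with intercept, position, context and intervention. Add intervention x context, intervention x position, or both. The interaction is separable only to the extent that the rank rises when intervention x context is added to a model already holding intervention x position.

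| Layout | Main effects | + intervention x context | + intervention x position | + both | Separable df |
|---|---|---|---|---|---|
| Trials 1 and 2, set order | 7 | 16 | 16 | 16 | 0 of 9 |
| Trial 3, set order | 3 | 4 | 4 | 4 | 0 of 1 |
| Trials 1 and 2, 4 x 4 context orders | 10 | 19 | 19 | 28 | 9 of 9 |
| Trial 3, 2 x 2 context orders | 4 | 5 | 5 | 6 | 1 of 1 |

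Under the set order the two interactions span the same space. In Trials 1 and 2, the sequence-group and first-order carry-over terms (3 df each) also lie inside it. Of the 9 df, 3 are free of both, but none is free of position.

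**Trial 3 by hand.** Group 1 sees arm A in context 1, then arm B in context 2. Group 2 sees B in context 1, then A in context 2. The interaction is (A1 - B1) - (A2 - B2) = (A1 + B2) - (B1 + A2), which is the sum for group 1 minus the sum for group 2. It is therefore the difference between the two sequences.

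Take assumed illustrative values: a baseline mean of 3.5 on the 5-point scale and an effect of 0.4. Each of these three mechanisms gives the same four means, 3.5, 3.9, 3.5, 3.5 (group 1 first and second message, group 2 first and second message):
- B gains 0.4 in context 2;
- B gains 0.4 as the second message;
- having seen A first raises the second response by 0.4.

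The estimated interaction is (3.5 + 3.9) - (3.5 + 3.5) = 0.4 each time.

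**What cancels.** If the second message loses the same amount in both arms, both group sums fall equally and the interaction does not move. Only position effects that differ by arm matter.

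**Why varying the order works.** Crossing the four combinations with four Latin-square context orders puts each intervention/context/position triple in the design once: 4 x 4 x 4 = 64 cells from 16 flows of four messages. Trial 3 has 2 x 2 x 2 = 8 cells from four flows of two. There, intervention x context contrasts flows {A1B2, B2A1} with {B1A2, A2B1}. Intervention x position and carry-over contrast A-first {A1B2, A2B1} with B-first {B2A1, B1A2}. The two contrasts are orthogonal.

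**The case against.** The set order is deliberate and disclosed. The Objective lists who speaks, imagery, format and delivery, and no context-specific effect. The Analysis section introduces the interactions only after setting context comparisons outside the primary analysis. Messages are short (videos of up to 2 minutes, one session), and levels are spread over contexts partly to limit contamination between them. Complete aliasing does not make the rival explanations equally plausible: if no position effect differs by arm and, in Trial 3, there is no carry-over, the interaction can be read as intended. The documents give no size for such effects.

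All of this stands, and it limits the consequence. It does not remove the problem. The disclosure covers contrasts between contexts only, the assumption needed to read the interactions is nowhere stated, and neither a larger sample nor another model can test it under the set order.

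Three stronger readings are tempting, and the documents do not support them:
- **The main comparisons are biased.** Intervention levels are balanced over position, so the set order does not touch them. Carry-over that differs by arm could reach the Trial 3 main contrast, but it would do so under any context order.
- **Fatigue or novelty in general spoils the interaction.** What is common to all arms cancels.
- **The low precision of the Trial 3 interaction measures this defect.** With variance s² per response, correlation r within a participant and n participants, the interaction has variance 8s²(1 + r)/n against 2s²(1 - r)/n for the main contrast. The ratio 4(1 + r)/(1 - r) is 16.5 at r = 0.61 and 7.4 at r = 0.3. Each participant sees each arm in only one context, so this is a between-participant contrast whatever the order, and the ratio is unchanged by the fix. The factor 4 comes from the difference-of-differences scale (without it: 4.1 and 1.9), and the protocol gives 0.61 for paired proportions, not for Trial 3 scores. The ratio should not be used as a measure of the set-order problem.

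**Conclusion.** The concern holds for the intervention-by-context interactions of the Analysis section. They are completely aliased with intervention-by-position effects in all three trials and, in Trial 3, also with the sequence difference and carry-over. The result rests only on the set order and the number of combinations that the text states, and it holds for any set order. How much a given finding would mislead depends on arm-specific position effects, or carry-over, of unknown size. Intervention main effects and intervention-by-population interactions are unaffected by the set order. This is a limited but avoidable defect in a supplementary analysis: as written, the Design and Analysis sections do not fit together on this point.

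**What to change.** Vary the context order in the Qualtrics survey flow. In Trials 1 and 2, cross the four combinations with four context orders from a Latin square (16 flows); in Trial 3, cross the two combinations with two context orders (4 flows). Record position, and fit context and position as fixed factors, each with its interaction with intervention.

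Videos, survey items and sample size stay as they are. The cost is building and checking more flows in every subgroup survey and language version (Dari, Sinhalese and Auslan among them). In a subgroup of 40, the flows in Trial 1 would hold 40/16 = 2.5 participants on average, against 40/4 = 10 now, so context interactions are better examined pooled over subgroups. In Trial 3 the interaction becomes separable but remains imprecise.

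If the order cannot be changed, add a sentence to the Analysis section: the context interactions are exploratory combined context/position effects (in Trial 3 also sequence and carry-over), and no context-specific conclusions will be drawn from them.
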